**Documentation of eligibility**

|                                                                                                               |                                                                                            |                                                                                            |                                    |
|---------------------------------------------------------------------------------------------------------------|--------------------------------------------------------------------------------------------|--------------------------------------------------------------------------------------------|------------------------------------|
| Participant's Study ID number                                                                                 |                                                                                            |                                                                                            |                                    |
| N
o.                                                                                                       | Questions and filters (variable names)                                                     | Coding categories                                                                          | Skip                        |
| 1                                                                                                             | What is your date of birth?                                                                | __/__/__
(dd/mm/yy)

77 Incomplete date

99 Declined to answer              | If complete date, skip to 3 |
| If month and day are unknown, use 15 May. If year is unknown, ask for age and calculate year of birth. |                                                                                            |                                                                                            |                                    |
| 2                                                                                                             | Calculated date of birth?                                                                  | __/__/__
(dd/mm/yy)                                                                     |                                    |

| 
If yes to both questions 3 and 5, participant is still eligible; please continue with eligibility questions.
 
If not eligible, thank the elderly for his or her time and let them know they are ineligible for the study.
 |                                                                       |                                                          |  |
| 6. Have you received the influenza vaccine in 2015?                                                                                                                                                                                                  |                                                                       | 1 Yes
2 No                                            |  |
| 
If yes, end the questionnaire and thank elderly for his or her time and let them know they are ineligible for the study.
                                                                                                               |                                                                       |                                                          |  |
| 7. Are you here to receive the influenza vaccine this year?                                                                                                                                                                                          |                                                                       | 1 Yes
2 No
77 Do not know
99 Declined to Answer |  |
| 
If replied with no, do not know, or declined to answer, thank elderly for his or her time and let them know they are ineligible for the study
 
If answered Yes, ask the following questions:
                              |                                                                       |                                                          |  |
| 8. Are you allergic to egg, or do you have any known allergy or negative reaction to the flu vaccine?                                                                                                                                                |                                                                       | 1 Yes
2 No
3 Do not know                           |  |

|                                                                                                                                                                                                                                                                       |               |
|-----------------------------------------------------------------------------------------------------------------------------------------------------------------------------------------------------------------------------------------------------------------------|---------------|
| 9. Do you have any medical condition that could prevent your full participation in having blood drawn?                                                                                                                                                                | 1 Yes
2 No |
| If replied with yes to either question 8 or 9, thank elderly and let participant know they are not eligible for the immunogenicity part of the study. If answered No to both 8 and 9, please inform participant about immunogenicity study and ask for consent |               |

**Documentation of consent for Immunogenicity study**

|                                                                                     |                                                                                                                                            |
|-------------------------------------------------------------------------------------|--------------------------------------------------------------------------------------------------------------------------------------------|
| Participant has read and signed the informed consent form for Immunogenicity study? | 1 Yes
2 No                                                                                                                              |
| If no, please specify the reason for refusal. _____                          |                                                                                                                                            |
| If yes, ask the following baseline questions and record the following data   |                                                                                                                                            |
| Participant's Identification Number (to obtain Influenza records)                   |                                                                                                                                            |
| Participant's Study ID number                                                       |                                                                                                                                            |
| Participant's HN number                                                             |                                                                                                                                            |
| 10. When, if ever, have you received the influenza vaccine in the past?             | Please circle all that apply:
0 Never
1 Last year
2 2 to 4 years ago
3 5+ years ago
77 Do not know
99 Declined to answer |

|                                                                                                                                                                                                                           |                                                                                                                                                                     |
|---------------------------------------------------------------------------------------------------------------------------------------------------------------------------------------------------------------------------|---------------------------------------------------------------------------------------------------------------------------------------------------------------------|
| 
11. Do you have any conditions that make you immunocompromised (For example, chemotherapy, bone marrow or organ transplant, steroid medications, etc.)?
                                                            | 
1 Yes
 
2 No
 
77 Do not Know
 
99 Declined to answer
                                                                                         |
| 
Fill out blood titer appointment sheet with participant and record appointment dates for our records
                                                                                                        | 
1st blood draw/vaccine _____
 
2nd blood draw _____
 
3rd Blood draw _____
 
4th blood draw _____
 |
| 
Tell participant, "Thank you for your time and for enrolling in the immunogenicity study."
 
Direct participant about where to go to have blood drawn prior to obtaining the influenza vaccine.
 |                                                                                                                                                                     |

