### **2. Secondary Objectives**

2.1: Measure the effect of SARI and ARI on change in functional status

2.2: Evaluate duration of humoral immune response of IIV3 among persons aged 65 years and older; and compare difference in humoral immune response by number of past influenza vaccinations

2.3: Measure the incidence of respiratory syncytial virus in persons  $\geq 65$  years

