([http://support.sas.com/documentation/cdl/en/statug/67523/HTML/default/viewer.htm#statug\\_power\\_overview.htm](http://support.sas.com/documentation/cdl/en/statug/67523/HTML/default/viewer.htm#statug_power_overview.htm)) to calculate the required sample sizes. Assuming a mean score of 4 for the controls and 5 for the cases (higher VES-13 index indicates lower functional status), and standard deviation of 3 for the difference between the two means, a type I error rate of 0.05, correlation of 0.2 and power of 80%, we require 115 in matched pairs (230 in all).

Sample size for seroconversion: Seroconversion for secondary objective 2.2 will be assessed in a sub-sample of participants. We expect seroconversion rates of 30-50% among those vaccinated. In order to calculate a proportion of 50% plus or minus 5%-pts, we need 384 individuals who intend on becoming vaccinated. We will enroll them sequentially.

$$\frac{[Np(1 - p)]}{d^2 / 1.96^2 (N - 1) + p(1 - p)}$$

Where  $N$  is the population size,  $p$  is the estimated proportion,  $d$  is the absolute precision. In this study,  $N$  is the size of the elderly population in the two districts, approximately 15,000;  $p$  is 0.5 and  $d$  is 0.05.

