**For secondary objective 2.2 (Immunogenicity)**

Elderly who have not yet been vaccinated, but have presented to the district hospital for vaccination will be asked by trained study staff at the district hospital to join the immunogenicity subset of the study regardless of whether they joined the primary study. Elderly will be informed of the objective aim, protocol, risks and benefits of joining the immunogenicity study. If elderly consent, they will be asked to have blood drawn before being vaccinated with the inactivated, trivalent influenza IIV3 vaccine the same day (day 0), and return to the district hospital again to have blood drawn 28 days (1 month), 180 days (6 months) and 360 days (1 year) after receiving the vaccine. One additional blood draw will be requested after 28 days of second vaccination in the year 2 to compare the effect of prior vaccination on level of immunological response. For participants unable to travel to the health center, the research nurse will travel to the elderly participant's home and obtain the necessary blood sample, and transport the sample back to the district hospital in ice packs. Participants will be asked for 5cc of blood per scheduled appointment. The serum will be separated from the blood samples using a centrifuge at the district hospital and stored in a refrigerator between 4-8°C for a week or less. On a weekly basis, the serum samples will be transported in ice-packs for less than 24 hours to the NIH laboratory in Nonthaburi. When participants consent to being enrolled, the study staff that consents and enrolls them will also take an electronic baseline assessment questionnaire CRF that should take about 15 minutes to administer. They will provide the participant with a study ID card which has their individual study number and the days of their next scheduled appointments. The card will also have a number to call a study team member if the participant should need to reschedule their appointment or has any other issues or concerns.

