## **7.5.2 Participant selection method**

### Primary study

That Phanom and Plapak Districts have approximately 6,000 and 3,000 elderly members, respectively. There are 136 villages in That Phanom and 85 villages in Plapak. In order to maintain population proportions, approximately 2/3 of the 3,500 calculated necessary sample size will be chosen from That Phanom (about 2,333 individuals) and approximately 1/3 will be selected from Plapak (about 1,167 individuals). To get proportional representation, we will use systematic random sampling. The elderly will be sorted in this order: district, sub-district, village, 5-year age band. The sampling interval will be calculated as the total number of elderly residents divided by the total sample size. A random number will be selected from within the sampling interval as the starting point. The random start plus the sampling interval will be applied to the list to select the sample.

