To estimate the incidence of influenza-associated COPD exacerbations among elderly with COPD, we will calculate the total number of laboratory-confirmed influenza-associated COPD exacerbations per total number of COPD patients within our cohort over a year (primary objective 1.3). We will compare the incidence among those that were vaccinated with IIV3 versus those that were not vaccinated with IIV3. In order to account for correlation among repetitive measurements from each individual, we will also employ GEE methodology. This method will also allow us to adjust for underlying confounders such as smoking history and age.

Blood samples will be taken from a select number of participants who will have had IIV3 to test the antibody response of IIV3 among the elderly (objective 2.2). These blood samples will be taken at baseline before receiving the shot, and then again after 28 days (1 month), 180 days (6 months), and 360 days (12 months) later. The blood samples will be tested for HI antibodies. Everyone with a baseline HI assay  $\geq 10$  who has a four-fold increase in HI antibody count post vaccination or who has a baseline HI assay  $< 10$  who has a post vaccination count  $\geq 40$  will be considered seroconverted against influenza. One additional blood draw will be taken after 28 days of subsequent vaccination in the second year to compare the effect of prior vaccination on level of immunological response. We will use a random effects model (RE) to compare blood

samples at the post vaccination dates to the baseline HI assay to determine how long participants vaccinated with IIV3 retain an adequate number of HI antibodies. RE allows us to control for the differences in antibody count amongst all individuals across unequal intervals and obtain a mean distribution. This methodology will also allow us to control for confounders such as age and factors which make participants immuno-compromised.

We will also evaluate a simpler outcome, the incidence rate of RSV among elderly with ARI or SARI over the entire observation period (second-objective 2.3), which should be similar between those that were vaccinated with Influenza IIV3 and those that were not.

Aggregate results may be shared with relevant CDC programs in which the findings of this study may have immediate policy implications. Opportunities for publication will be sought.

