## **Limitations**

The main limitation of this study is its limited generalizability to Thailand. While we are able to obtain a representative sample of Nakhon Phanom Province, the people in NP may be different than people from other parts of Thailand. Another limitation is sampling bias. The study's sample may be biased since healthier people are usually more willing to participate in studies compared to people who are more ill, which would not represent the target population of all types of elderly people. In order to diminish the potential of sampling bias, our inclusion criterion includes all elderly despite illness type.

It is possible that not all respiratory events in the enrolled elderly will be captured, due to inability to communicate, misunderstanding and even memory loss. To a large extent, a lot of the success for this project may rely on the relationship between the household and health volunteer and role of the caregiver for participants greater than 80 years of age. Another limitation to our study is that baseline enrollment data and weekly follow-up data is relying heavily on self-report. It is possible for participants to be unaware of whether they have certain underlying co-

morbidities if they do not regularly visit the physician, it is possible for them to under or overestimate their functional status, and it is possible for them to forget to take a nasal self-swab or remember that they even experienced an ARI or SARI. In order to mitigate these potential issues, we are using a reliable and sensitive functional status questionnaire and following-up with participants weekly in case they forget to call us.

Although Thailand provides free vaccinations for elderly, there are not enough purchased to vaccinate all elderly in Thailand. Due to the limited number of vaccines, elderly that are sicker and see health care professionals more often are more likely to become vaccinated than those who are healthier. The elderly who join our immunogenicity study will most likely be sicker than the general population and are more likely to be immunocompromised. Because of this selection bias, our immunogenicity study will most likely show a lower rate of seroprotection among the elderly than what is actually representative of the average elderly population.

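### The immunogenicity enrolment form records no sex, chronic disease or functional status, so for most participants the between-person comparison by past vaccination can probably be adjusted only for age and immunocompromise

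*Protocol*

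**What the plan says.** Objective 2.2 (section 5) includes the aim to "compare difference in humoral immune response by number of past influenza vaccinations". Section 7.9 plans a random-effects model that will allow the analyst to "control for confounders such as age and factors which make participants immuno-compromised".

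Sections 7.5.3 and the appendix list give form 4h as the enrolment questionnaire for this sub-study. As printed, it covers age, date of birth, residence, vaccination in 2015, allergy, obstacles to blood draw, timing of past influenza vaccination, the item "Do you have any conditions that make you immunocompromised", a national identification number and the hospital number. Sex, diagnosed conditions and functional status are not on it; they are on cohort form 4b.

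On recruitment, section 7.5.1 (objective 2.2) says that people presenting for vaccination are asked to join the "immunogenicity subset of the study regardless of whether they joined the primary study". Section 7.5.2 takes the first 384 who consent, and section 7.2 does not make the two studies mutually exclusive. Section 7.10 reads differently: it describes the 384 as part of the 3,500 or more enrolled.

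On illness and vaccination, the Limitations section states that "elderly that are sicker and see health care professionals more often are more likely to become vaccinated than those who are healthier". The pilot-study text in section 3.1.4 says that vaccination in the province is aimed at elderly people with underlying chronic conditions. Section 4.2 reports that functional status can influence how well influenza vaccination works.

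**The concern.** The number of past vaccinations is not assigned, so comparing people by it is an observational contrast. If people vaccinated more often in the past are also the more chronically ill or frail, and illness or frailty lowers antibody response, a lower response in repeat vaccinees could be read as an effect of prior vaccination when part of it reflects health. That is the direction of effect that section 4.2 raises as a question.

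For the primary comparison, section 3.1.4 plans to control for baseline functional status and underlying conditions. For this comparison the same information is not collected from people outside the cohort. The choice of covariates can be left to an analysis plan, but a covariate that was never recorded cannot be added there.

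**Working it through.** **1. The plan's own figure.** Section 7.1.5 states: "In order to calculate a proportion of 50% plus or minus 5%-pts, we need 384 individuals who intend on becoming vaccinated". With p = 0.50 and d = 0.05, the formula without finite-population correction is n = 1.96² × p(1 − p) / d² = 3.8416 × 0.25 / 0.0025 = 384.16, that is, 384. The stated size is reproduced. The printed formula with its correction gives 374.6 (375) for N = 15,000 and 368.5 (369) for N = 9,000. The figure is therefore a precision for one proportion in the whole sample.

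**2. How many of the 384 would have form 4b.** The inputs are:
- Cohort size: 3,133 to be enrolled or, as an upper figure, the 3,500 to be selected (section 7.1.5).
- Elderly population: the protocol gives two values. In section 7.1.5, N "is the size of the elderly population in the two districts, approximately 15,000". In section 7.5.2, "That Phanom and Plapak Districts have approximately 6,000 and 3,000 elderly members, respectively", which sums to 9,000.
- Assumption: attendance at the vaccination clinic is independent of cohort selection.

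Expected overlap = 384 × cohort size / elderly population.

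| Cohort | Elderly | Share in cohort | With form 4b | Without form 4b |
|---|---|---|---|---|
| 3,133 | 15,000 | 20.9% | 80 | 304 (79%) |
| 3,500 | 15,000 | 23.3% | 90 | 294 (77%) |
| 3,133 | 9,000 | 34.8% | 134 | 250 (65%) |
| 3,500 | 9,000 | 38.9% | 149 | 235 (61%) |

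Under either population figure a majority lack form 4b. If section 7.10 is read literally, the number without it is zero.

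**3. What can be adjusted for.**

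| Factor | Form 4h | Form 4b |
|---|---|---|
| Age | yes | yes |
| Immunocompromise | yes (item 11) | yes (items 45-46) |
| Sex | no | yes (item 54) |
| Diagnosed chronic conditions | no | yes (items 33-48) |
| Functional status | no | yes (items 4 and 10-30) |

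**4. An illustration of size.** The documents give no figures for illness by vaccination history or for response by illness, so all four inputs are assumed: chronic disease in 60% of repeat vaccinees and 30% of the never vaccinated; seroconversion 35% with chronic disease and 50% without.
- Repeat vaccinees: 0.6 × 0.35 + 0.4 × 0.50 = 41.0%.
- Never vaccinated: 0.3 × 0.35 + 0.7 × 0.50 = 45.5%.
- Spurious difference: (0.6 − 0.3) × (0.50 − 0.35) = 4.5 points, with no true effect of prior vaccination.

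The difference falls to zero if illness does not vary with vaccination history or does not alter response. The yardstick is the precision of a two-group difference. With an even split of 192 and 192 (the best case), the 95% half-width is 1.96 × √[(0.41 × 0.59 + 0.455 × 0.545) / 192] = 1.96 × 0.0505 = 9.9 points. The assumed bias is under half of that.

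**The case against.** **The named confounders are collected.** A reader might infer that the protocol fails to record the confounder it names. It does not fail in this. Section 4.2 names age as the confounder of prior vaccination and response, section 7.9 names age and immunocompromise, and form 4h records both. This objection stands in full. The gap concerns factors that the protocol discusses elsewhere and does not name for this analysis.

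**The Limitations text is about who is vaccinated at all.** All 384 are vaccinees. That illness also varies with the number of past vaccinations among them is a plausible inference, not a statement in the protocol. This stands, and it is one reason why the size is unknown.

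**The data could be obtained later.** A reader might infer that they are lost for good. Form 4h holds a national identification number and a hospital number, medical records are reviewed elsewhere in the study, and participants return for further draws with a new consent before day 360. Sex and long-standing diagnoses could therefore be recovered. No such step is planned, however. The identification number is there to obtain influenza records, and section 7.7 deletes identifying data after cleaning. VES-13 is self-reported, so records are unlikely to supply functional status as it was at vaccination.

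**There is a within-person comparison.** The extra draw 28 days after the second-year vaccination lets the same person's two responses be compared, which holds sex and stable illness constant. This stands: that part of objective 2.2 is less affected. It does not replace the comparison across people with different vaccination histories.

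**Covariates belong in the analysis plan.** The list in section 7.9 is open-ended, and naming covariates there is optional. Collecting them is a matter for the form.

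**Conclusion.** The point holds as a gap in data capture for the between-person comparison in objective 2.2. Chronic illness, frailty and sex could be adjusted for in about 80 to 149 of the 384, or in more only through unplanned linkage. That range rests on independence between clinic attendance and cohort membership, and on the protocol's two population figures. It is an expectation, not a stated fact, and it fails if section 7.10 is the governing text.

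The documents do not support a claim that the comparison will be materially biased. The 4.5-point illustration uses assumed inputs. A reader might set it against the stated ±5 points, but that precision is for a single proportion; for a difference between two groups the half-width is about ±10 points at best. The objective is secondary, and this is a cheap improvement rather than a fault that invalidates the sub-study.

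**What to change.** - Add sex, the physician-diagnosed conditions (form 4b items 33-48) and the VES-13 items to form 4h. Section 7.5.1 already plans a baseline interview of about 15 minutes for this sub-study.
- Use these as covariates in the between-person comparison by past vaccination in section 7.9.
- Reconcile section 7.10 with sections 7.5.1 and 7.5.2 on whether the 384 are drawn from the cohort.

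The cost is some minutes more per enrolment. Before conditional skips it is 16 condition items, about 22 functional-status items (4 and 10-30 on form 4b) and one item for sex. The protocol puts VES-13 at under five minutes on average and says that it is already translated into Thai.
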